##### Acquisition protocol

Magnetic resonance imaging was performed at all participating centres using 3-Tesla MRI scanners, following a shared, harmonised acquisition framework specifically developed for the BIOMIGA project. Across the three sites (Pavia, Hamburg and Barcelona), the MRI protocol systematically included the same core set of sequences: (1) High-resolution three-dimensional T1-weighted structural imaging (3D T1); (2) Resting-state functional MRI (rs-fMRI); (3) Arterial spin labelling (ASL) perfusion imaging. Before proceeding with the analysis, all images were defaced locally to anonymise the dataset.

These sequences were selected to enable integrated assessment of brain morphology, functional connectivity and cerebral perfusion, which are all implicated in migraine pathophysiology and CGRP-related mechanisms.

At the coordinating centre in Pavia, MRI data were acquired on a 3.0 T Siemens Skyra scanner (Siemens Healthineers, Erlangen, Germany) equipped with a 32-channel head coil. The acquisition protocol comprised: (1) a high-resolution 3D T1-weighted scan (MPRAGE; TR/TE = 2300/2.98 ms, flip angle = 9°, 240 slices, FOV = 256 mm, voxel size = 1.0 mm^3^ isotropic) for anatomical reference and morphometric analyses; (2) resting-state fMRI (rs-fMRI) using a T2*-weighted gradient-echo echo-planar imaging (GRE-EPI) sequence (TR/TE = 2330/26 ms, voxel size = 2.0 mm^3^ isotropic, FOV = 256 mm, 34 slices, 305 volumes); (3) arterial spin labeling (ASL) using a 3D Turbo Gradient Spin Echo (TSGE) pseudo-continuous ASL (pCASL) sequence (TR/TE = 3000/22.56 ms, inversion time (TI) = 1800 ms, FOV = 256 mm, 42 slices, 2 measurements [1 label/ 1 control]).

At the coordinating centre in Barcelona, MRI data were acquired on two 3.0 T Siemens systems (Tim Trio and MAGNETOM Prisma, Siemens, Erlangen, Germany). The Tim Trio was equipped with a 32-channel phased-array head coil, whereas the MAGNETOM Prisma used a 64-channel head–neck coil. The acquisition protocol comprised: (1) a high-resolution 3D T1-weighted scan (MPRAGE; TR/TE = 2300/2.98 ms, FOV = 256 mm, 192 slices, voxel size = 1 mm^3^ isotropic); (2) resting-state fMRI (rs-fMRI) using a T2*-weighted GRE-EPI sequence (TR/TE = 2330/26 ms, voxel size = 2.0 mm^3^ isotropic, FOV = 224 mm, 34 slices, 305 volumes); (3) arterial spin labeling (ASL) using a 3D TSGE pCASL sequence (TR/TE = 3000/22.56 ms, TI = 1800 ms, FOV = 256 mm, 42 slices, 2 measurements [1 label/1 control], voxel size = 1.0 × 1.0 × 2.5 mm^3^).

In Hamburg, MRI data were acquired on a 3.0 T MAGNETOM Prisma scanner (Siemens Healthineers, Erlangen, Germany) equipped with a 32-channel head coil. The acquisition protocol comprised: (1) a high-resolution 3D T1-weighted scan (MPRAGE; TR/TE = 2300/2.98 ms, flip angle = 9°, 240 slices, voxel size = 1 mm^3^ isotropic, FOV = 256 mm); (2) resting-state fMRI (rs-fMRI) using a T2*-weighted GRE-EPI sequence (TR/TE = 2330/26 ms, voxel size = 2 mm^3^ isotropic, FOV = 256 mm, 34 slices, 305 volumes); and (3) arterial spin labeling (ASL), including a 3D TSGE pCASL sequence (TR/TE = 3000/22.56 ms, TI = 1800 ms, FOV = 256 mm, 42 slices, 2 measurements [label/control]) and an additional 2D pulsed ASL (PASL) sequence (TR/TE = 3000/12.0 ms, TI = 1800 ms, FOV = 256 mm, 21 slices, 90 measurements [45 label/45 control]).

To account for multicentric variability, scanner site was explicitly modelled as a covariate in all group-level neuroimaging analyses, and dedicated quality-control procedures were applied to ensure consistency of spatial coverage, artefact burden and temporal signal characteristics across centres. All datasets underwent local anonymisation and active defacing before central storage and processing.

Details of pre- and post-processing are going to be integrated in future publications.

Additionally, BOLD activation imaging using an event-related fMRI pain paradigm were carried out in an independent subset of 25 CM patients, before and after treatment, to investigate treatment-related modulation of trigeminovascular and brainstem pain-processing circuits. To this end, we used an adapted imaging protocol with a nociceptive stimulation paradigm designed to engage the trigemino-thalamic and spino-thalamic pathways, with a particular focus on brainstem nuclei involved in migraine pathophysiology, including the spinal trigeminal nucleus, periaqueductal grey, locus coeruleus and dorsal raphe complex. This paradigm was adapted from previously validated high-resolution brainstem fMRI protocols and optimised to detect subtle changes in nociceptive processing and descending pain modulation. The experimental design allowed investigation of afferent sensory processing as well as efferent modulatory mechanisms, testing the hypothesis that peripheral blockade of the CGRP receptor by erenumab induces measurable central changes in pain-related brainstem and thalamo-cortical networks.

To complement central neuroimaging findings with a peripheral functional readout, the same subgroup underwent assessment of neurovascular skin responses to controlled thermal stimulation. A moderate heat stimulus (40 °C) was applied to the left volar forearm, and the resulting axon-reflex-mediated vasodilatory flare was quantified using laser speckle contrast imaging (PeriCam PSI System®, Perimed Instruments, Sweden). This approach provides a non-invasive measure of peripheral CGRP-dependent neurovascular reactivity. By investigating both task-based fMRI of the brain and peripheral neurovascular measurements, this experimental model aimed at bridging molecular blockade at the periphery with functional reorganisation of central pain networks.

### Statistical analysis

#### Efficacy endpoint analyses

The primary objective of the study is to identify a panel of biomarkers that is reliably associated with response to treatment in a substantial proportion of patients with migraine. To this end, we will develop classification algorithms that assign patients to response categories defined on an ordinal scale. Supervised machine-learning approaches based on parametric, semi-parametric and non-parametric models are going to be fitted and compared. The optimal model will be selected according to predefined performance criteria, including area under the curve (AUC), accuracy, precision and recall.

Secondary analyses will characterise differences between migraine patients and healthy controls at baseline in: (i) DNA methylation profiles; (ii) structural and functional magnetic resonance imaging measures; and (iii) pharmacogenetic, biochemical, clinical and psychological variables. Within the migraine cohort, we will also compare DNA methylation, brain morphometry and functional connectivity, as well as pharmacogenetic, biochemical, clinical and psychological measures, among patients classified as responders and non-responders to CGRP-targeting mABs.

Given the prospective design, changes in clinical status, disability and psychometric measures, from baseline to the end of the treatment period, are going to be evaluated to quantify the impact of the therapy and to relate these changes to treatment response categories. In parallel, longitudinal differences in structural and functional magnetic resonance imaging measures among response groups are going to be examined to identify treatment-related brain changes and estimate their effect sizes in relation to drug exposure and clinical improvement (e.g., reduction in monthly headache days).

Finally, plasma concentrations of CGRP, IL-1β and TNF-*α*, together with their messenger RNA expression in peripheral blood mononuclear cells, are going to be assessed over the course of treatment to explore treatment-related alterations in peripheral inflammation and their correlation with clinical endpoints, including headache frequency, acute medication intake and disability.

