##### Machine learning (ML) algorithms

As the primary modelling approach, RF classification was selected because it is well suited to high-dimensional biomedical datasets, can model non-linear relationships and interactions among predictors, and provides internal estimates of generalisation error through out-of-bag (OOB) samples. RF models is going to be trained using bootstrap aggregation, with random feature selection at each node split. Hyperparameter tuning will consider the number of trees, the number of variables sampled at each split, tree depth and terminal node size; final values are going to be selected according to cross-validated/OOB performance. RF-derived feature-importance measures are going to be used to rank predictors according to their contribution to classification performance. This approach is consistent with recent migraine studies using ML to predict response to anti-CGRP monoclonal antibodies (26, 28).

To assess the incremental predictive value of multimodal data integration, RF models are going to be developed using a progressive feature expansion strategy. Models are going to be trained and compared using: (i) clinical and biochemical variables; (ii) clinical, biochemical, and genetic variables; (iii) clinical, biochemical, genetic, and epigenetic variables; (iv) clinical, biochemical, genetic, epigenetic, and structural MRI variables; and (v) the full multimodal dataset including clinical, biochemical, genetic, epigenetic, structural MRI, and functional MRI (fMRI) features. This sequential approach will quantify the added predictive contribution of each data modality and reduce the likelihood that model performance is driven by a single data source or modality-specific confounding effect.

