Following this initial phase, a stricter feature-selection step based on RF importance rankings is going to be applied to identify a reduced and more informative feature subset. This reduced feature space will then be used to train and compare additional supervised machine-learning algorithms, including:Support vector machine (SVM): Linear and radial-basis-function kernels are going to be considered to test whether response categories can be separated by maximum-margin decision boundaries in the selected feature space. The regularisation parameter and, for radial-basis-function kernels, the gamma parameter is going to be tuned within the inner validation loop. SVMs have previously been applied to migraine classification using clinical and neuroimaging-derived variables (40).Artificial neural network (ANN): simple feed-forward multilayer perceptron models are going to be considered to capture potential non-linear relationships among multimodal predictors. Given the limited sample size, the ANN architecture is going to be intentionally parsimonious, with tuning of the number of hidden units/layers, regularisation strength and learning rate, and with early stopping where appropriate to reduce overfitting. Neural-network approaches are included as exploratory non-linear benchmark models in line with the broader use of artificial intelligence methods in migraine research (29).k-Nearest Neighbour (kNN): Distance-based classification is going to be applied after appropriate scaling of continuous predictors. The number of neighbours and distance metric are going to be selected within the training folds. kNN will serve as a simple, non-parametric benchmark model that classifies subjects according to similarity with neighbouring cases in the reduced multidimensional biomarker space (41)Decision Tree: classification-tree models are going to be used as interpretable non-linear classifiers able to represent threshold-based combinations of predictors. Tree depth, minimum node size and pruning/complexity parameters are going to be tuned to limit overfitting. Decision-tree models will also provide a clinically intuitive comparator to ensemble methods such as RF and AdaBoost (40)AdaBoost: adaptive boosting models based on weak decision-tree learners are going to be considered to assess whether sequential reweighting of misclassified observations improves classification. The number of estimators, learning rate and base-tree complexity are going to be are going to be tuned within the inner validation loop. Boosting approaches, including AdaBoost, have previously been used in migraine classification studies combining questionnaire and imaging-derived variables (40, 42, 43, 54).

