
#### Model evaluation and validation

These models are going to be evaluated within a nested cross-validation framework, with inner loops for hyperparameter tuning and outer loops for performance estimation, to ensure an unbiased assessment of generalisation performance. All transformations, feature-selection procedures, class-balancing strategies and hyperparameter optimisation steps are going to be confined to the training folds and then applied to the corresponding validation/test folds. For RF models, predictive performance will also be assessed using the out-of-bag (OOB) error rate, which provides an internal estimate of generalisation performance without the need for a separate validation set. OOB misclassification rates and class-specific OOB errors are going to be examined as global and category-specific performance indicators. For models evaluated using cross-validation, performance is going to be quantified using a combination of metrics, including balanced accuracy, sensitivity, specificity, positive and negative predictive values and area under the receiver operating characteristic curve (AUC), allowing comparison across algorithms in the presence of class imbalance.

This multi-step modelling strategy was designed to balance predictive performance, robustness and interpretability in the context of a complex, high-dimensional biomarker dataset. Because the final model specification depends on the observed data structure and on the retained feature set, the complete algorithmic configuration, selected hyperparameters and final validation results are going to be reported in the subsequent results manuscript. A schematic overview of the machine-learning pipeline, including preprocessing, feature selection, model training, validation and performance evaluation, is provided in Figure 3. This workflow illustrates the sequential and nested structure of the analysis and highlights the measures adopted to minimise overfitting and information leakage.

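### If the best algorithm is picked on its cross-validated performance, that same performance is not an unbiased estimate for the winner; the article assigns the inner loop only to hyperparameter tuning

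*Protocol article*

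**What the plan says.** All references are to the protocol article.

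- **Selection rule.** Efficacy endpoint analyses, on the primary objective: "The optimal model will be selected according to predefined performance criteria, including area under the curve (AUC), accuracy, precision and recall".
- **Role of the loops.** Model evaluation and validation describes nested cross-validation "with inner loops for hyperparameter tuning and outer loops for performance estimation, to ensure an unbiased assessment of generalisation performance". The cross-validated metrics are then given the purpose of "allowing comparison across algorithms in the presence of class imbalance".
- **What is nested.** The same section says: "All transformations, feature-selection procedures, class-balancing strategies and hyperparameter optimisation steps are going to be confined to the training folds". Choice of algorithm is not on that list.
- **Candidates.** Machine learning (ML) algorithms: "As the primary modelling approach, RF classification was selected". Also, "RF models are going to be developed using a progressive feature expansion strategy", over five cumulative modality sets. After a feature-selection step based on random-forest (RF) importance, "This reduced feature space will then be used to train and compare additional supervised machine-learning algorithms": SVM, neural network, kNN, decision tree and AdaBoost.
- **RF tuning.** "final values are going to be selected according to cross-validated/OOB performance". Model evaluation and validation also reports out-of-bag (OOB) error as an internal measure of generalisation that needs no separate validation set.
- **Caveat.** Limitations and future directions concedes that there is no independent validation cohort and that OOB and cross-validated estimates may be too favourable in complex multicentre data.

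**The concern.** Nested cross-validation gives a close to unbiased estimate for a procedure whose every data-driven choice is repeated inside the training folds. If several such procedures are ranked on their outer-fold results and the best is reported with the result that made it best, the ranking itself has used the test folds. The winner's figure then contains part of its own favourable sampling error.

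The article describes no other place where the algorithm is chosen. The inner loop has one stated task (hyperparameters), the list of nested steps omits algorithm choice, and the metrics used for comparison are those reported.

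OOB error for RF raises the same issue on a smaller scale: it may be the tuning criterion and is also a reported performance measure.

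The headline AUC of the selected panel is at stake. The models are meant to prioritise predictors for validation in larger cohorts, and a validation study planned around an inflated figure would start from too favourable an assumption.

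**Working it through.** The article states no target or expected AUC, so there is no figure of its own to reproduce. The size of the effect has to rest on assumptions.

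**Inputs**
- Patients: 168 with 6% loss (Sample size calculation), so 168 × 0.94 = 157.9, about 158 evaluable.
- Class split: assumed 50% responders, so 79 versus 79. As a smaller case, 47 versus 47, the group size in the same section.
- Candidates: K = 6, that is RF plus five further algorithms, with the SVM kernel counted as a tuning choice. K = 10 if a winner is also taken among the five RF modality sets (5 RF models + 5 other algorithms).
- Correlation ρ between the candidates' AUC estimates: not given; 0.5 to 0.8 assumed.

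**Step 1: standard error of one AUC under no signal**

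SE = √[(n₁ + n₀ + 1) / (12 n₁ n₀)]

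- 79 v 79: √[159 / (12 × 79 × 79)] = 0.0461
- 47 v 47: √[95 / (12 × 47 × 47)] = 0.0599

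**Step 2: expected excess of the best of K equally good, equally correlated estimates**

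Excess = SE × √(1 − ρ) × E[max of K standard normals], where E[max] = 1.267 for K = 6 and 1.539 for K = 10.

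| Classes | K | ρ = 0.8 | ρ = 0.5 |
|---|---|---|---|
| 79 v 79 | 6 | 0.0461 × 0.447 × 1.267 = 0.026 | 0.0461 × 0.707 × 1.267 = 0.041 |
| 79 v 79 | 10 | 0.032 | 0.050 |
| 47 v 47 | 6 | 0.034 | 0.054 |
| 47 v 47 | 10 | 0.041 | 0.065 |

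**Step 3: algorithms that truly differ**

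Equal true performance is the unfavourable case. With six algorithms at 79 v 79 whose true AUCs are spread evenly over ±0.05, the winner's observed AUC exceeds its own true AUC by about 0.012 at ρ = 0.8 and 0.026 at ρ = 0.5 (simulated).

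**Step 4: check by simulation on pure noise**

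Five-fold cross-validation was run 500 times with feature screening inside each training fold, six simple classifiers standing in for those listed, and five cumulative feature blocks.

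| Classes | Single pre-fixed model | Best of 6 algorithms | Best of 10 |
|---|---|---|---|
| 79 v 79 | 0.500 | 0.539 | 0.568 |
| 47 v 47 | 0.500 | 0.551 | 0.589 |

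A model fixed in advance recovers the true 0.500, so in-fold feature selection works as intended. The excess comes only from picking the best. Fold number, feature counts and classifiers are assumptions here; the article does not give them.

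**The case against.** Several objections carry weight.

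- **The step is inferred.** No sentence says that the final choice uses outer-fold results or that the winner's outer-fold figure is the headline. A condensed article may leave the exact place of algorithm choice to a fuller document. This stands as a limit on certainty. But the article itself allots the loops, states the selection rule and makes the claim of unbiasedness, and no other mechanism appears in it.
- **Feature selection.** A reader might infer that features too are chosen on the reported performance. The text does not support this: Preprocessing and feature selection, and Model evaluation and validation, both confine it to training data. The five modality sets are presented as a way to measure added value, not as competitors for one winning place. The firm count is therefore six candidates. Reaching 10 or 11 requires counting modality sets, or both SVM kernels, as competitors.
- **RF as primary approach.** A reader might see a contradiction with picking an optimal model. The neural network, kNN and decision tree are described as benchmarks or comparators, which is compatible with RF being primary. What remains is that the selection rule does not say whether RF stays the headline if another algorithm ranks first.
- **Metrics.** The section on class imbalance rules out relying on overall accuracy alone; it does not bar accuracy. The criteria are called predefined, so a priority may exist elsewhere. Still, one list has plain accuracy and the other balanced accuracy, and the article ranks none.
- **Already disclosed.** The models are labelled exploratory, and the limitations admit possible optimism and the need for replication. That lowers the stakes. The caveat is general, however, does not name model selection, and contradicts the claim made in the validation section.
- **Size.** The excess is at most about one standard error of a single AUC in the six-algorithm case at 79 v 79, and less when algorithms differ. This is correct.

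**Conclusion.** The concern holds in a limited form. Followed as written, the plan makes the selected algorithm's reported outer-fold performance optimistic, and describing it as unbiased is not supported for the winner. For six equally good algorithms at 79 v 79 the optimism is about 0.026 AUC (ρ = 0.8) to 0.041 (ρ = 0.5). It falls to about 0.012 to 0.026 if true AUCs are spread over ±0.05, and rises to about 0.032 to 0.050 if a winner is also taken across the RF modality sets with all candidates equal. These figures assume a binary 1:1 outcome with 158 evaluable patients. The article plans ordinal, imbalanced categories, so they indicate scale only. The conclusion rests on reading the selection rule together with the loop roles.

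OOB error that has served for RF tuning should likewise not be presented as an independent performance measure; the size of that effect was not computed.

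**What to change.** 1. Choose one of two routes. Either report RF on one pre-declared modality set as the headline result whichever algorithm ranks first, and label all other models as benchmarks. Or make the choice of algorithm (and of modality set, if one is to be chosen) inside the inner loop, so that the outer loop scores the whole procedure.
2. Name one deciding metric that is robust to imbalance, for example AUC in a form suited to the response scale used. Treat the others as descriptive and use the same list in both sections.
3. Report the performance of every candidate, not only the selected one.
4. Do not report OOB error as generalisation performance where it was used for tuning.
5. If none of this is adopted, withdraw the claim of unbiased assessment in Model evaluation and validation and bring it into line with the limitations section.

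The cost is wording, some computing time and a slightly lower reported AUC. Status of the study says that processing for the stratified groups is still under way, so the change can be made without new data.

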### Interventions

#### Subjects living with HFEM or CM

They are assessed at baseline, then they receive a 3-month course of treatment with erenumab, a mAb targeting the CGRP receptor. The choice to use erenumab was dictated by the fact that it was the first and, at the time the trial began, the only CGRP-targeting mAb available on the European market.

No concomitant migraine preventive treatment was allowed during the screening, baseline and the 3-month treatment period. Abortive medications were allowed, but the type and formulation had to be the same throughout the study. Their usage was registered as well.

Their responders/non-responder status was defined assessed at the end of the 3-month treatment cycle, based on the headache diary data. Patients were classified as responders (R) if they achieved a ≥50% reduction in monthly headache days (MHD) during the final 4 weeks of the 12-week erenumab treatment period compared with the 4-week baseline run-in period. Patients who achieve a <50% reduction in MHD were classified as non-responders (NR). Within the R group, super responders (SR) were defined as patients who achieve a ≥ 75% reduction in MHD over the same period. Within the NR group, full non-responders (FNR) were defined as patients who achieve a < 25% reduction in MHD over the same period.

At visit 1, inclusion/exclusion criteria were reviewed; demographics and clinical characteristics were recorded. To avoid sample heterogeneity and to identify and minimise confounding factors, all participants underwent a structured interview to collect demographic information, including age, sex, ethnicity; clinical information including habits of caffeine, tobacco and drug consumption, physical activity level; life-time comorbidities, medication use, menstrual status and migraine-related information.

At this visit, participants started recording their headache characteristics in an *ad hoc* diary for a month to confirm the diagnosis at the following visit.

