At visit 2, participants performed the following procedures:Diagnosis confirmation based on data recorded in the diary;Assessment of migraine-related disability, psychometric variables, quality of life, comorbidities, acute medications intake and Emergency Room Use in the previous month;Venous blood samples for DNA extraction for DNA methylation analysis for CGRP-related polymorphisms, and for biochemical profiling;Neuroimaging evaluation: 3 T Magnetic resonance imaging (MRI), including structural, resting state MRI (rsMRI), Arterial Spin Labelling (ASL) using a standardised protocol provided by UKE.

Once the assessment was completed, participants were administered the first 140-mg dose of erenumab. Upon discharge, the patient received 2 additional 140-mg doses of the drug, a training on the modality of self-injection and the schedule for self-injection (one dose every 28 days).

Visits 3 and 4 were remotely conducted to collect data from diaries, clinical scales and verify that the patients managed to self-inject the drug properly.

At visit 5, participants under:Assessment of treatment efficacy through the headache diaries and stratification of based on the response to treatment;Assessment of treatment satisfaction with validated patient-reported outcomes (PROs, listed in Table 1 and detailed in the next paragraph);Assessment of migraine-related disability, psychometric variables, quality of life, comorbidities, acute medications intake and Emergency Room use in the previous month; Assessment of epigenetic, biomolecular and neuroimaging parameters only for the SR and FNR subgroups.

**Table 1 tab1:** Scheduled activities for subjects with migraine and healthy controls.

	Subjects living with migraine					Healthy subjects
	Baseline (4 wk)	Treatment period				All activities were performed at visit 2
	Day 0	Day 1	Wk + 4	Wk +8	Wk +12 End of observ	
Visit number	1	2	3*	4*	5	
Informed consent	X					X
Pregnancy test	X	X				
Headache diary explained and given to patient	X	X	X	X	X	
Headache diary data collected		X	X	X	X	
Demographics, medical & headache history	X					X
Physical and neurological examination & vital signs	X				X	X
Adverse events		X	X	X	X	
Concomitant medications	X	X	X	X	X	
Blood samples§	X				X**	X
Neuroimaging	X				X**	X
Dosing		X	X	X		
MIDAS		X			X	
HIT-6		X			X	
BAI		X	X	X	X	X
BDI-II		X	X	X	X	X
MIG-SCOG		X			X	
MSQ		X			X	
PGI-I		X	X	X	X	

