* Remote visit; ** Only for super responders and full non-responders. MIDAS, Migraine Disability Assessment; HIT-6, Headache Impact Test-6; BDI-II, Beck Depression Inventory-II; BAI, Beck Anxiety Inventory; MSQ, Migraine-Specific Quality of Life Questionnaire; MIG-SCOG, Migraine-Specific Cognitive Impairment Scale; PGI-I, Patient Global Impression of Improvement. § Pharmacogenetic polymorphisms, plasma levels of CGRP and cytokines.

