#### Healthy controls

These subjects were only assessed at baseline (visit 2) to verify satisfaction of inclusion and exclusion criteria.

Once enrolled, blood samples were collected from the antecubital vein for DNA extraction for DNA methylation analysis for CGRP-related polymorphisms and for biochemical profiling. All subjects also underwent neuroimaging evaluation with 3 T Magnetic resonance imaging (MRI), including structural, resting state MRI (rsMRI), and Arterial Spin Labelling (ASL) using a standardised protocol provided by UKE.

The protocol design is illustrated in Figure 2, scheduled activities for subjects with migraine and healthy controls are summarised in Table 1.

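### Week-12 biomarkers come only from the two extreme response groups, so planned correlations with headache-day reduction would overstate the whole-cohort values, and an effect size related to drug exposure cannot be estimated

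*Protocol article*

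**What the plan says.** Under Interventions (Subjects living with HFEM or CM), "super responders (SR) were defined as patients who achieve a ≥ 75% reduction in MHD over the same period", and "full non-responders (FNR) were defined as patients who achieve a < 25% reduction in MHD over the same period". The visit 5 list in that section includes "Assessment of epigenetic, biomolecular and neuroimaging parameters only for the SR and FNR subgroups". The Table 1 footnote attached to week-12 blood samples and neuroimaging repeats the limit: "Only for super responders and full non-responders".

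Under Statistical analysis, Efficacy endpoint analyses, the longitudinal MRI sentence plans to examine differences among response groups "to identify treatment-related brain changes and estimate their effect sizes in relation to drug exposure and clinical improvement (e.g., reduction in monthly headache days". The next paragraph follows plasma CGRP, IL-1β and TNF-α and their mRNA over treatment "to explore treatment-related alterations in peripheral inflammation and their correlation with clinical endpoints, including headache frequency, acute medication intake and disability". Neither sentence mentions that follow-up values exist for two groups only.

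On exposure, the visit 2 description gives every patient one 140-mg dose and hands out two more. For healthy controls the article says: "These subjects were only assessed at baseline (visit 2) to verify satisfaction of inclusion and exclusion criteria".

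**The concern.** Patients with a reduction from 25% to under 75% have no follow-up biomarker by design. The selection is made on MHD reduction, the variable that the MRI sentence names as its example of clinical improvement. Keeping only the two ends of that variable enlarges its variance, and a correlation computed there is larger than the correlation among all treated patients. A reader who takes the reported coefficient as the whole-cohort value would overestimate the strength of the relation, and a validation study sized on it would be too small.

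The exposure claim is a separate problem. Without variation in planned exposure and without an untreated group measured twice, an effect size for exposure has nothing to be estimated from. Before-after change would carry a treatment label that the design cannot support.

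**Working it through.** **Share of patients without follow-up biomarkers.** The Sample size calculation section gives 47 per group, 6% loss and a 30% rate of response above 75%. It mentions the rate of response below 25% in the same sentence without a figure of its own. Applying 30% to each extreme reproduces the stated total closely:

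- 47 / 0.94 = 50 per extreme group, and 50 / 0.30 = 166.7, so 167 against the stated 168.
- Controls: 47 / 0.94 = 50, against the stated 51.

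I therefore use 30% for each extreme.

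- Completers: 168 × 0.94 = 157.9.
- With week-12 biomarkers: 157.9 × 0.60 = 94.8, about 95.
- Without: about 63, or 40%.

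**Effect on a correlation with MHD reduction.** Assume a bivariate normal relation and selection of the lower and upper share q. With c the standard normal quantile at 1 − q and φ the normal density, the variance ratio of MHD reduction in the selected sample is

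u = [c·φ(c) + q] / q.

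At q = 0.30, c = 0.524 and φ(c) = 0.348, so u = (0.182 + 0.300) / 0.300 = 1.61.

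The correlation in the selected sample is r′ = r·√u / √(1 + r²(u − 1)).

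| True r | r′ | True r² | r′² | Overstatement of r² |
|---|---|---|---|---|
| 0.20 | 0.25 | 0.040 | 0.063 | 57% |
| 0.30 | 0.37 | 0.090 | 0.137 | 52% |
| 0.50 | 0.59 | 0.250 | 0.349 | 40% |

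A simulation of 1,000,000 pairs gave the same r′ (variance ratio 1.60). Spearman's coefficient behaves alike: 0.29 becomes 0.36 where the true Pearson r is 0.30. In the same simulation the regression slope of the biomarker on MHD reduction stayed at 0.30. By the formula, a true r of 0 stays 0.

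**Sensitivity to the tail shares.** Other shares are my assumptions. For a true r of 0.30:

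- 40% lower and 30% upper: u = 1.39, r′ = 0.35.
- 20% in each tail: u = 2.17, r′ = 0.42.

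**Other endpoints.** Let ρ be the correlation of disability change with MHD reduction, s that of the biomarker change with MHD reduction, and r the true biomarker-disability correlation. After selection,

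r′ = [r + ρs(u − 1)] / √{[1 + s²(u − 1)]·[1 + ρ²(u − 1)]}.

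As an illustration, take ρ = 0.5 and r = 0.30:

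- s = 0.15: 0.346 / 1.081 = 0.32.
- s = 0.30: 0.391 / 1.102 = 0.35.

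This is less inflation than the 0.37 for MHD reduction itself.

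**Exposure.** There are two ways to read the term.

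- *Between patients:* the planned course is three 140-mg doses for everyone, so planned exposure has zero variance. It could differ only through missed self-injections, and the article describes no drug level or adherence measure as an exposure variable.
- *Before versus after:* healthy controls are measured once and there is no placebo or untreated patient group. Change cannot be separated from time, retest effects or placebo response.

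**The case against.** Several objections have force.

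- **The MRI sentence already compares response groups.** Read with the visit 5 restriction, this amounts to super-responders versus full non-responders. That stands, and the contrast is legitimate. But the same sentence goes on to promise effect sizes in relation to MHD reduction and exposure, with no restriction stated.
- **The word correlation is used only for the blood markers, as exploration.** This stands. A reader might infer that longitudinal methylation correlations or a pooled mean change are also planned; the article states neither.
- **Extreme-group sampling creates no association with MHD reduction where none exists.** This stands. The slope is unbiased if the relation is linear, and the test keeps its size. What is affected is the standardised coefficient.
- **The size is uncertain.** The lower 30% is inferred, percentage reduction cannot exceed 100%, so normality is approximate, and inflation is smaller for disability and acute medication. All of this stands, and it limits the figures to an indication.
- **The design is already conceded as open-label and non-randomised.** Limitations and future directions does say so. It does not mention the extreme-group sampling, and the statistical section still claims an effect size for exposure.
- **An analysis plan that is not shown may settle slope versus correlation.** It may. The point here is what the article states: an exposure effect that the design cannot deliver, and clinical relations described without the restriction.
- **Some patients are scanned before and after treatment regardless of response.** The 25-patient chronic migraine task-fMRI and skin-flare subset is not stated to be selected on response, so the sampling point does not extend to it. It too lacks an unexposed comparator.

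**Conclusion.** The point holds for secondary and exploratory longitudinal analyses in the main cohort. If 30% of patients fall in each extreme and the relation is bivariate normal, a true correlation of 0.30 with MHD reduction would read about 0.37 (0.35 to 0.42 over the other tail shares tried). About 40% of patients contribute no week-12 biomarker. An effect size in relation to drug exposure cannot be estimated under either reading of the term.

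A reader might go further and infer that the longitudinal findings would be spurious, or that R² would double. The documents do not support either. The test of no association with MHD reduction is sound, and a doubling needs 20% tails, which the article does not give. Nor does the article say that results from the two extremes will be presented as those of all treated patients; it is silent on the point. The primary aim, classifying patients into response categories, is not touched by this argument.

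**What to change.** In Efficacy endpoint analyses:

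1. State that main-cohort longitudinal biomarker analyses are contrasts between super-responders and full non-responders.
2. For relations with MHD reduction, report regression slopes, or correlations corrected for selection using the MHD-reduction distribution of the whole cohort, which the diaries supply. Label any uncorrected correlation as applying to the two extreme groups only.
3. Delete the reference to drug exposure, and replace treatment-related with change during treatment.

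I would not prescribe baseline adjustment of the change scores. The groups are not randomised and may differ at baseline, which is the study's own hypothesis, so that choice is a trade-off for the authors.

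The cost is wording and a standard correction. No new data are needed, and the article reports that processing for the stratified analysis is still under way. Reported standardised associations will be smaller.
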